#### Craving

The Mannheimer Craving Scale (MaCS) (38) is a self-report questionnaire with 12 items, assessing substance-related urges to consume psychoactive substances/drugs. Items are based on a five-point scale with item-specific verbatim for each point, e.g., item 11: “How strong is your urge to take the substance? 0 = I feel no urge, 1 = I feel some urge, 2 = I feel a strong urge, 3 = I feel a very strong urge, 4 = The urge is absolutely overwhelming and cannot be influenced.”

#### Substance use

Substance use is assessed via structured interview (5) by a clinical psychologist who asks for the number of use days and the amount per use day on average for each of the following substances both for past month and past year: nicotine, alcohol, cannabis, methylenedioxymethamphetamine (MDMA), amphetamine, methamphetamine, hallucinogens, opiates, inhalants, or other. These quantity and frequency reports are multiplied to obtain a quantity-frequency index (e.g., for alcohol: 10 drinking days past month × 4 standard drinks per drinking occasion = 40 consumption units per month during the past year). Additionally at BL, the interviewer will ask the same questions for past year-use as well as for age at first use per substance. Changes in the past-month quantity-frequency index for tobacco use will be a primary outcome. Other substances are only explored given that youth welfare institutions do not permit any other substance use than smoking.

#### Subjective utility

For adolescents, a self-designed questionnaire (“Gruppenevalution Jugendliche,” GEJ) from the DELTA evaluation study (15) will be used. The questionnaire contains 20 items that are related to SUD-specific subjective utility as trained in the group sessions (e.g., “I recognize my triggers,” “I’ve learned to deal with boredom,” “I have more control over my SUD,” and “I have more drug knowledge”). Items are rated on a five-point Likert scale (0 = does not apply at all, 1 = applies a bit, 2 = applies rather than not, 3 = applies most of the time, and 4 = applies always) to indicate how much participants approve each statement.

For personnel, a comparable self-designed questionnaire (“Gruppenevalution Betreuer,” GEB) was designed. One part asks for changes in subjective utility (GEB-K) induced by the one-day workshop, e.g., “I feel that I have learned new skills for coping with the child,” “I feel less alone with the substance use problems of the child,” “I feel I have gained more control over the current substance use problems of the child.” Personnel is instructed to rate it is approval for each of the 14 GEB-K statements using the same five-point Likert scale as the GEJ. The second part asks for the satisfaction (GEB-S) with the workshop, separately for organizational aspects (eight items, five-point Likert-scale from 1 = does not apply at all to 5 = absolutely applies, e.g., “The trainer was well-prepared,” “Material was well-designed and could be readily used”) and for applicability of workshop content to their daily work (six items, five-point Likert-scale from 1 = not helpful at all to 5 = very helpful, e.g., “Comorbid disorders,” “Stages of recovery”). GEB-K and GEB-S have been used during the piloting of the DELTA evaluation study (15).

#### Additional measures

Current DSM-5 diagnoses for SUDs as well as co-occurring mental disorders are assessed with the Mini-International Neuropsychiatric Interview for Children and Adolescents (MINI-KID) (35) or the Childrens’ Diagnostic Interview for Mental Disorders (C-DIPS) (61, 62) depending on license availability. Both instruments are structured interviews for DSM-5 disorders in children and adolescents with substantial to almost perfect interrater and test–retest reliability (35, 61).

Sociodemographic characteristics of adolescents are acquired via questionnaire from legal guardians, including information on participant’s age (in years), gender, parental school education (list of school graduation options), and relationship status of biological parents. Sociodemographic characteristics of personnel is obtained via standardized questions regarding age (in years), gender, school education (list of school graduation options), and current SUD-related subjective utility (percentage, from 0 = ‘none at all’ to 100 = ‘all you must know’).

Adherence to therapy is operationalized through the number of sessions attended by each adolescent (ranging from 1 to 16 sessions, with more sessions indicating stronger adherence) and by subjective rating of active participation by each adolescent itself (five-item questionnaire, GTS-P) (34). Although participants are instructed to attend to all 16 weekly sessions as well as individual sessions, thus only participants with one or more attended sessions will be analyzed. The study team member who conducts a group session will additionally rate how well the group participated actively in each respective session, and whether any adverse events occurred (nine-item questionnaire, GTS-T) (34). Drop-out from the study as well as discharge of adolescents from an institution will be recorded by study personnel.

Substance use motives specifically for smoking are assessed via the Motives Questionnaire Revised for Smoking (MQ-RS), an instrument we developed. The MQ-RS uses the 20 items and the five-point scale [ranging from 1 = (almost) never to 5 = (almost) always] from the established drinking motives measure of Cooper in its revised form (45). In contrast to drinking motive measure, we had to reword items 8 (“…about not smoking” instead of “…about not drinking”) and 10 (“…to feel the kick” instead of “…to get high”) in order to avoid alcohol-specific or smoking-unrelated wording.

Using a breath analyzing device, we will measure the amount of carbon monoxide (CO) in breath in accordance to standards in the field (63), with CO ≤ 20 ppm indicating point abstinence from tobacco smoking (22).

The physical examination is carried out by medical students who is supervised by a principal investigator. Participants are measured (height in cm, weight in kg) and examined according to clinical routines. Any deviations from normal physical development are noted in a protocol, e.g., visible wounds, signs of diseases, or basic neurological problems. Adolescents will be asked for current infections, diseases, and medications. In case of psychoactive medication or acute infectious diseases, saliva and blood will not be collected or analyzed, as these factors a confounding issues.

### Data management

Data quality is checked biannually via interim analysis and auditing by the principal investigators regarding outliers, subgroup means, and missing data patterns of primary and secondary outcome data, with the final decision to terminate the trial if applicable. As in the previous DELTA evaluation study, missing item values will be replaced by the mean of questionnaire items, if 80% or more of the items were answered (15). Items that may not be replaceable have been anticipated to appear in approx. 10% of the cases. The sample size estimation accounts for this by loss, see Figure 2.

### Data analysis

Analyses will be conducted with the most recent version of the software “IBM SPSS Statistics,” currently version 27.0. Adolescents are analyzed as randomized if they participated in at least one DELTA session (DELTA condition only). To test all non-descriptive hypotheses (see below, hypotheses 2–4), a repeated measures MANOVA will be conducted using time as factor (“within factor”) given the explanatory nature of the trial and the non-importance of between-group effects. A significant reduction over time (BL vs. FU) in all *N* = 40 participants across all metric outcomes (MaCS score, FTND score, DUDIT score, AUDIT score, and cigarettes per day during the past month according to substance use interview) indicates a relevant intervention effect. This multivariate approach will limit the chance for false-positive results as otherwise possible due to multiple testing. Effect sizes will be classified into small effects (ƞ^2^ ≥ 0.01), medium effects (ƞ^2^ ≥ 0.06), and large effects (ƞ^2^ ≥ 0.14). In case of severe non-normality of outcome variables, we will have to apply non-parametric tests instead of the repeated measures MANOVA.

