**Figure 1 fig1:**
[figure not shown]
Overall study schedule and timeline.

To achieve the outlined aims, we conceptualized an explanatory three-stage study over the course of 24 months, see Figure 2 for the 24-month study schedule. After adjusting the DELTA manual (12), to feedback from youth welfare institution personnel (content analysis of semi-structured qualitative interviews) in the adjustment stage, participants are cluster-randomized (institution as cluster, allocation by unblinded principal investigator who assigns the group consecutively to the sequence “intervention-waitlist-intervention-waitlist”) to either one of two study arms [immediate treatment condition vs. waiting list control group condition (WL) with SUD treatment after 16 weeks] during the sampling stage. In terms of the Medical Research Council Framework for the evaluation of complex interventions (23), this design can be considered a pragmatic trial in “phase 2,” which implies that theoretically relevant aspects have been previously identified (pre-clinical research, phase 0) (12), and that components of interventional procedures are readily available (modeling research, phase 1) (12). Further elements of a pragmatic trial are a simplified analysis design and uncontrolled environments (24). Blinding of participants, care providers, outcome assessors, or analysis is not feasible in this trial. In sum, the chosen design significantly differs in several relevant aspects from ‘classical’ cluster-randomized RCT (phase 3).

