### Interventions

#### DELTA intervention before revision

The manualized DELTA intervention (12) aims to reduce substance use and SUD-related problems to obtain abstinence and general well-being. It combines motivational interviewing, contingency management, cognitive-behavioral, and systemic therapy, see Table 2. Weekly group sessions of 60-min with 3–8 adolescents are led by up to two psychologists, who also conduct up to eight individualized 1-on-1 sessions (30 min) for each participant. Group sessions follow a structured plan including recurring elements (past-week craving review, checking homework, setting session goals, session-specific content, getting new homework, mindfulness exercise or reflection and feedback, and sporadic urine testing) and session-specific work sheets, but it also includes role plays, presentations, white-board actions, written self-evaluations, experimentation with skills boxes, mindfulness exercises etc. Attendance of all sessions is required and formally accepted within a signed “therapy contract.” Exemptions from sessions need an *a-priori* explanation (e.g., doctor’s appointment). When two or more meetings were missed without a valid explanation, or a sporadic drug urine test was positive on two occasions, adolescents have to be temporally excluded from group sessions for 8 weeks. Re-entry into the group sessions was possible after 8 weeks or a consultation with the attending therapist.

**Table 2 tab2:** Intervention content of the DELTA intervention before revision.

Session	Topic	Goal(s)
Adolescent patients group		
1.	Use and motivation to stop	Link substance use to SUDs Discover personal abstinence motivation
2.	Triggers	Identify triggers for craving and relapse
3.	Skills	Explore anti-craving skills
4.	New challenges	Develop situational anti-relapse strategies
5.	Relapse and stress	Reduce stress to prevent relapses
6.	Self-esteem	Develop self-esteem
7.	Honesty	Develop honesty in substance use self-reports
8.	Depression	Prevent and cope with depressiveness
9.	Boredom	Prevent and cope with boredom
10.	Understanding emotions	Identify emotions and associated reactions
11.	Coping with emotions	Promote activities to evoke positive emotions Avoid activities/situations associated with negative emotions
12.	Relapse justifications	Avoid situations with relapse risk
13.	Anti-relapse training	Revisit relapse prevention strategies, especially “3. Skills”

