#### Estimation of sample size

Sample size will be optimized to achieve sufficient power for hypothesis testing. Assuming an error probability of α = 0.05, test power of 1−β = 0.95, a large effect of time with *f* = 0.40, and a repeated measures correlation of *r* = 0.1, we computed minimum sample sizes of *N* = 40 analyzed adolescents and *N* = 40 analyzed personnel with the G*Power software (64). Large effect sizes were anticipated given that the actual intervention effect size (15) had not yet been analyzed at the time of the inception of DELTA-JU and the proposal for funding and ethics approval in 2020.

Considering the dropout rates from BL to FU for adolescents (assuming 20%) and personnel (assuming 10%), at least *N* = 50 adolescents and *N* = 45 personnel will have to be included at BL. In case that dropout rates exceed 20%, we will continue to sample participants in order to achieve the required analysis sample size of *N* = 40 nonetheless as long as study funding is available. For qualitative interviews, a sample size of *N* = 10 was deemed as an adequate compromise between resources and expected output.

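### The time-only MANOVA and the N = 40 sample size treat adolescents who live and are treated together as independent; if their changes are correlated within groups, type I error rises above 5% and a valid test falls short of 0.95 power

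*Protocol article*

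**What the plan says.** Study design states that "participants are cluster-randomized (institution as cluster", and Sampling stage calls the allocation group-wise. On delivery, the section on the intervention before revision says "Weekly group sessions of 60-min with 3–8 adolescents are led by up to two psychologists"; Sampling stage allows changes after the revision. Setting specifics in content describes adolescents living full-time in the institution under a common routine and supervision.

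For hypotheses 2–4, Data analysis says "a repeated measures MANOVA will be conducted using time as factor". The comparison is BL against FU, pooled over all 40 participants, on five metric outcomes: MaCS, FTND, DUDIT, AUDIT and cigarettes per day. Between-group effects are declared unimportant, and the multivariate approach is justified as limiting false positives.

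Estimation of sample size opens with "Sample size will be optimized to achieve sufficient power for hypothesis testing". The calculation rests on four inputs: a power of 0.95, a 5% error level, 0.1 for the correlation between the two measurements, and "a large effect of time with *f* = 0.40". They lead to 40 analysed and, with 20% dropout, 50 included. The article gives no number of groups, ICC, design effect or cluster term.

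**The concern.** Members of one therapy group share sessions, therapists, peers and house rules between BL and FU. Smoking, one of the primary outcomes, is a social behaviour that the house rules partly permit. If such influences move a whole group up or down together, the 40 change scores carry less information than 40 independent ones.

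A test that ignores this uses too small a standard error and rejects too often when nothing has changed. This is the only inferential test behind Aim C, and the article reads a significant result as a relevant intervention effect. The 0.95 power was also computed for independent observations, so it would not carry over to a test that allows for the grouping.

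**Working it through.** **1. The plan's own figure.** Inputs from Estimation of sample size: α = 0.05, power 0.95, f = 0.40, r = 0.1, two time points.

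- Noncentrality: λ = N·2·f²/(1 − r). At N = 40: 40 × 2 × 0.16/0.9 = 14.22, with 1 and 39 df.
- Power is 0.957 at N = 40 and 0.952 at N = 39, so N = 40 reproduces to within one participant.
- Inclusion: 40/0.8 = 50, as stated.
- The equivalent standardised mean change is dz = 0.40 × √(2/0.9) = 0.596.

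The arithmetic is correct, with a design effect of 1.

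**2. Which correlation counts.** The test uses FU minus BL within each person. A constant difference in level between institutions drops out. What remains is the ICC of the change scores within a group.

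**3. Assumptions, because the document gives no figures.** ICC of change 0.01 to 0.20. 40 adolescents in 8 groups of 5; groups of 3–8 would give about 5 to 13 groups. Correlation between the five outcomes 0.3.

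**4. Formulas.** Design effect DE = 1 + (5 − 1) × ICC; effective N = 40/DE. Type I error is simulated (20,000 to 40,000 trials per setting) for the planned test without a cluster term: a single-outcome F test, and Hotelling's T² for five outcomes. Power is for a single outcome at dz = 0.596. The design-effect version uses λ = 14.22/DE with 39 df; the t-test on group means uses the same λ with 7 df.

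| ICC | DE | Effective N | Type I error, one outcome | Type I error, five outcomes | Power, planned test | Power, design effect only | Power, t-test on 8 group means |
|---|---|---|---|---|---|---|---|
| 0 | 1.00 | 40.0 | 0.050 | 0.048 | 0.957 | 0.957 | 0.896 |
| 0.01 | 1.04 | 38.5 | 0.054 | 0.059 | 0.955 | 0.950 | 0.885 |
| 0.05 | 1.20 | 33.3 | 0.070 | 0.094 | 0.946 | 0.919 | 0.838 |
| 0.10 | 1.40 | 28.6 | 0.095 | 0.150 | 0.930 | 0.874 | 0.780 |
| 0.20 | 1.80 | 22.2 | 0.144 | 0.278 | 0.907 | 0.783 | 0.676 |

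Repeat simulations agree within about one percentage point (for example 0.27 to 0.28 in the last five-outcome cell).

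**5. Fewer, larger groups.** With 5 groups of 8 and ICC 0.10, DE = 1 + 7 × 0.10 = 1.70. Type I error is 0.131 for one outcome and 0.242 for five. The t-test on 5 group means has power 0.59, but it has only 0.80 at ICC 0.

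**6. Splitting the power loss.** With 8 groups, moving to group means costs 0.957 − 0.896 = 0.061 before any correlation. A further 0.896 − 0.838 = 0.058 is lost at ICC 0.05, and 0.896 − 0.780 = 0.116 at ICC 0.10.

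**7. Check on a simple remedy.** Five separate valid tests on group means, each at 0.05 with no correction, give about a 21% chance of at least one false positive (outcome correlation 0.3). That exceeds the 9–15% of the planned MANOVA at ICC 0.05–0.10, so a change of method must bring its own error control.

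**The case against.** The strongest reply is that a within-person contrast already removes institution effects, and that nobody has shown that changes are correlated. The first half stands for stable differences in level, but not for influences acting on a whole group between BL and FU. The second half also stands: the ICC is unknown, and at 0.01 the planned test is close to nominal (about 5–6%).

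Some stronger inferences should be resisted.

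- A reader might take cluster allocation itself as the fault. The planned test compares no arms, so what matters is shared living and delivery, not how the groups were assigned.
- A reader might cite the remark in Strengths and limitations on the limited homogeneity of institutions. It is offered as a reason for replication elsewhere and says nothing about correlated change.
- The group size of 3–8 belongs to the manual before revision and may differ in DELTA-JU.
- The article plans no confidence intervals, so the charge is about p-values and power.

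It can also be said that this is a phase 2 pragmatic study with a deliberately simple analysis. Strengths and limitations does set aside baseline adjustment, subgroup, intention-to-treat and sensitivity analyses. It does not mention non-independence, and the trial still claims tests at p < 0.05 and 0.95 power.

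**Conclusion.** The point holds conditionally. The article fixes a test and a sample size that are right only if 40 adolescents in shared groups change independently of one another. For any positive ICC of change, the direction of the error is certain; its size is not.

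With 8 groups of 5 and outcome correlation 0.3, type I error runs from near nominal at ICC 0.01 to about 14% (one outcome) and 27% (five outcomes) at ICC 0.20. It is worse with fewer, larger groups.

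A reader might infer that the 5% level and 0.95 power definitely fail. The documents do not support that, because they give neither the ICC nor the number of groups. Nor does the planned test lose much power: it keeps about 0.91–0.95 because it rejects too readily. Power falls when the test is made valid, and for a test on group means part of the fall is lost degrees of freedom.

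**What to change.** - In Data analysis, replace the time-only MANOVA with an analysis of BL–FU change that accounts for the cluster: the therapy group, nested in institution if one institution runs several groups. Options are a mixed model with a random cluster effect on change and small-sample degrees of freedom, or a t-test on cluster-mean changes.
- Keep error control across the five outcomes, for example Holm or a pre-specified order, because the single multivariate test is being given up.
- In Estimation of sample size, state the expected number and size of groups, and restate the power at N = 40 over a range of ICC that includes low values such as 0.01. The power figures above are for one outcome at 0.05; Holm would lower them for an individual outcome.

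The cost is revised wording and a lower stated power, wider uncertainty, and variance components that are imprecise with few groups. No extra enrolment is required if the lower power is accepted. Holding 0.95 with 8 groups of 5 as the starting point would instead need 46 analysed at ICC 0.05 or 54 at ICC 0.10 by design effect alone (58 or 68 included).

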#### Waiting list control group

Participants whose group was cluster-randomized to the WL condition are not offered group sessions until 16 weeks have passed. During this period, adolescents may seek any kind of treatment as usual, including medication for co-occurring disorders or any kind of SUD treatment. Afterwards, DELTA-JU is provided in the same way as in the immediate treatment condition described above. The pre-treatment waiting period acts as a naturalistic comparator to the treatment. It is a suitable comparator given that many of the possible confounders (housing, timespan since previous detoxification treatment, availability of concurrent treatments/medication, psychosocial support, schooling situation etc.) should be equally present or absent in both conditions. Since concomitant treatments are allowed and documented in both conditions, we will be able to control for this confounder while at the same time providing a comparator group that represents the heterogeneity of SUD care in this population.

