#### Hypotheses

Aim (A) is reached when for each need, identified through qualitative analyses of interviews, one or more adjustments to the content or procedure of DELTA-JU is documented. No quantitative hypothesis is applicable. Aims (B) and (C) are achieved through testing the following hypotheses in adolescents who are abstinent for alcohol and drugs except nicotine/tobacco:
Adolescents: relevant increase in SUD-related subjective utility through FU (descriptive: a medium rating of 2.0 or higher in the respective GEJ items across participants);Adolescents: significant reduction of substance-related craving as a measure of relapse risk (*p* < 0.05, MaCS score) through FU;Adolescents: significant reduction of SUD severity (*p* < 0.05, scores of FTND, AUDIT, and DUDIT) through FU;Adolescents: significant reduction of self-reported past-month tobacco use through FU (*p* < 0.05, substance use interview);Personnel: relevant increase in SUD-related subjective utility through FU (descriptive: a medium rating of 2.0 or higher in the respective GEB items across participating personnel); andPersonnel: high satisfaction ratings concerning the workshop organization (descriptive: a medium rating of 4.0 or higher in the respective GEB items across participating personnel).

Additionally, secondary outcomes in adolescents (BDI-II, PQ-16, UCLA-PTSD, PSS-10, and SWLS) and personnel (ERI-S-10) will be tested exploratorily for changes through FU as previously done in the DELTA evaluation (15). All reductions through FU in adolescents are expected to be descriptively larger than reductions over the natural course, i.e., from PRE to BL in the WL group.

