### Strengths and limitations

The presented study design has several strengths. First, it is in line with ethical requirements that all adolescents are offered treatment. Waiting for 16 weeks in the WL condition still seems adequate given that adolescents may reside for up to 2 years in youth welfare institutions. In randomized clinical trials, for example, only cases may have received treatments. Second, it requires a smaller sample when participants become part of several analysis groups (intervention vs. WL). Third, alternative explanations of time effects may be controlled for by comparing BL-FU effects with PRE-BL effects.

Challenges arise from uncontrolled parallel treatments during the waiting period. Such treatments cannot be included in the quantitative estimation of treatment effects due to the limited number of participants in each group. Furthermore, homogeneity of cooperating youth welfare institutions is limited. Results may thus have to be replicated in other and diverging institutions. Although the sample size was *a-priori* calculated to maximize the use of available resources, drop-out rates may be unexpectedly high. In this case, additional participants and institutions may have to be recruited. In case of limited sample size, using Bayesan methods instead of testing for differences from zero may be advisable (74). Both the AUDIT and DUDIT have been previously used to assess changes in alcohol- and drug-related problems in adolescents and young adults using 3-month intervals between BL and FU (75, 76). Nevertheless, it remains possible that small changes in problems might go unnoticed given that both instruments cover 12 month periods. Another limitation arising from the limited sample size in a phase II study is the impossibility to adjust for several baseline variables. Such superior analysis strategies are not feasible at this point of the intervention development but will be imperative during phases III/RCT and phase IV studies in the future. The same holds true for the analysis of relevant patient subgroups (e.g., differentiating those with primarily alcohol-related problems from those with primarily cannabis-related problems) and intention-to-treat analyses or sensitivity analysis. Finally, additional measures that would objectify relapse to the use of alcohol or other drugs were not funded and will have to be implemented in a future trial, preferably a multi-center RCT testing DELTA-JU against treatment-as-usual.

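### The effectiveness rule reads a pooled before-after change as an intervention effect, although a waitlist arm is measured over the same weeks

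*Protocol article*

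**What the plan says.** Under Data analysis, "a repeated measures MANOVA will be conducted using time as factor" for hypotheses 2–4 (craving, SUD severity, tobacco use). Arm is not a factor, and the reason given is "given the explanatory nature of the trial and the non-importance of between-group effects". The decision rule follows: "A significant reduction over time (BL vs. FU) in all" 40 participants, across MaCS, FTND, DUDIT, AUDIT and cigarettes per day, "indicates a relevant intervention effect".

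Elsewhere the article describes a controlled design:

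- Study design: institutions are the clusters, and an unblinded principal investigator "assigns the group consecutively to the sequence" intervention, waitlist, intervention, waitlist.
- Table 1: both arms are assessed at week 0 and again at week 17. Week 17 is follow-up for the immediate arm and baseline for the waitlist arm.
- Sampling stage: the waitlist's extra PRE assessment is there to control for natural development.
- Waiting list control group: "The pre-treatment waiting period acts as a naturalistic comparator to the treatment".

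The waitlist data appear in two further places. Hypotheses says "All reductions through FU in adolescents are expected to be descriptively larger than reductions over the natural course", meaning PRE to BL in the waitlist group. Strengths and limitations says that "alternative explanations of time effects may be controlled for by comparing BL-FU effects with PRE-BL effects".

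**The concern.** A pooled change from baseline to follow-up contains the intervention effect plus everything else that happens over 16 weeks in a supervised, structured residence. The rule treats the sum as the intervention effect. The comparison that could separate the two is described but does not enter the rule: it has no threshold and cannot overturn a significant pooled result.

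The article itself supplies one mechanism for decline without treatment. AUDIT and DUDIT each cover the past 12 months (Severity of SUDs), and residents are generally abstinent from the start of their stay (Setting specifics in content). Between baseline and follow-up, about four months of earlier use can drop out of the recall window. Two of the five outcomes can then fall whether or not DELTA-JU works.

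At stake is the evidence for Aim C. Hypotheses says the aims are achieved by testing these hypotheses, and the Abstract makes dissemination conditional on effectiveness.

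**Working it through.** **Inputs from the protocol article (Estimation of sample size):** α = 0.05, power 0.95, effect of time f = 0.40, repeated-measures correlation r = 0.1, N = 40 analysed, 20% dropout. **Assumed, because the document gives no figure:** natural change of 0.2, 0.3 or 0.5 SD; r up to 0.5; correlation of 0.3 between the changes in the five outcomes; 20 analysed per arm; 8 institutions of 5; ICC 0 to 0.10.

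**1. The plan's own figure.** For a within-subject F test with two time points, λ = f² × N × 2 / (1 − r), on 1 and N − 1 df.
- N = 39: λ = 0.16 × 39 × 2 / 0.9 = 13.87, power 0.952.
- N = 40: λ = 14.22, power 0.957.
- Dropout: 40 / 0.8 = 50.

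The stated N = 40 and N = 50 are therefore sound for the test planned. They concern the effect of time only.

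**2. Chance of a significant reduction when the intervention does nothing.** For a paired test, dz = d / √(2(1 − r)), noncentrality = dz × √40, 39 df, two-sided critical value 2.023.

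| Natural fall d | r = 0.1: noncentrality | P(significant fall) | r = 0.5: noncentrality | P(significant fall) |
|---|---|---|---|---|
| 0.2 SD | 0.943 | 0.149 | 1.265 | 0.234 |
| 0.3 SD | 1.414 | 0.281 | 1.897 | 0.456 |
| 0.5 SD | 2.357 | 0.633 | 3.162 | 0.869 |

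**3. Does the multivariate test protect?** The planned test covers five outcomes together. With the same fall d in each and correlation c = 0.3 between changes, Hotelling's test has λ = N × 5d² / [2(1 − r)(1 + 4c)], on 5 and 35 df.
- d = 0.3: λ = 4.55 (r = 0.1) or 8.18 (r = 0.5), giving 0.285 or 0.502.
- d = 0.5: λ = 12.63 or 22.73, giving 0.717 or 0.946.

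The MANOVA limits multiplicity, as the article says. It does not limit this bias.

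**4. What the controlled contrast can deliver.** With two time points, f = 0.40 is a change of 2 × 0.40 = 0.8 SD over time. Taking 0.8 SD as the difference between arms is an assumption of this review. Adjusting for baseline at r = 0.1 gives 0.8 / √(1 − 0.01) = 0.804. With 20 per arm the noncentrality is 0.804 × √10 = 2.543.
- Ignoring clustering (38 df): power 0.70.
- With 8 institutions of 5 (6 df), noncentrality = 2.543 / √(1 + 4 × ICC): power 0.57 (ICC 0), 0.50 (ICC 0.05), 0.44 (ICC 0.10).
- At a difference of 0.5 SD, ignoring clustering: power 0.34.

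**The case against.** The strongest defence is that the claims are modest and the waitlist is used. Aim C speaks of association. The Discussion makes dissemination to other institutions depend on independent replication. Study design places the trial in phase 2 and sets it apart from a classical cluster-randomised trial, and Strengths and limitations defers better analyses to later phases. Hypotheses publishes an expectation that treated reductions exceed the waitlist's, so a waitlist that improved equally would visibly contradict it. Natural decline is also not established. Stays can last up to two years, so residents need not be recently detoxified. Nicotine use did not fall in the earlier evaluation, and two of the five outcomes are tobacco measures.

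Much of this stands, and it rules out some stronger readings. A reader might infer that the waitlist is ignored, but it has a stated descriptive role. A reader might infer that dissemination would follow directly from the pooled test, but the Discussion adds the replication condition. A reader might infer that a natural fall of a particular size will occur, but the document gives no such figure. None of this reaches the sentence in Data analysis, which draws a causal conclusion from a pooled time effect and is unaffected by the descriptive comparison. Early phase and small numbers explain modest power. They do not turn a before-after change into an intervention effect, and the limitations listed do not concede that the time effect is uncontrolled.

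**Conclusion.** The decision rule is wrong as written. It can declare an intervention effect when the waitlist improved just as much. The size depends on natural change, which is assumed: 15–23% of null trials at 0.2 SD, 28–46% at 0.3 SD and 63–87% at 0.5 SD for one outcome, and similar figures for five outcomes under the correlation assumed above.

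Two further inferences are not supported. The sample size calculation is not in error, since N = 40 reproduces for the time effect. Nor does the controlled contrast rescue a confident efficacy claim at this size. Its power is at most about 0.70 at r = 0.1 even if 0.8 SD is taken as the between-arm difference, and about 0.44–0.57 with the assumed 8 institutions. Allocation alternates under an unblinded investigator, so the contrast is not cleanly randomised either. It is an estimate to be read with caution, but it addresses the right question.

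**What to change.** 1. Delete the sentence that a significant pooled reduction shows an intervention effect, and label the MANOVA as change over time.
2. Base any statement on effectiveness on the immediate-versus-waitlist difference at week 17, adjusted for the week-0 score, for each of the five outcomes. Give a 95% CI that accounts for institution as cluster.
3. For that contrast, include all allocated participants with data, whether or not they attended a session. Under the present one-session rule (Setting and participants; Data analysis), immediate-arm attenders would be compared with a waitlist not yet offered sessions.
4. Optionally add a mixed model over PRE, BL and FU with exposure and elapsed-time terms. It uses the waitlist's later treatment data but assumes a common time trend, so it supports the week-17 contrast and is not equivalent to it.
5. State that the 0.95 power applies to the time effect only, and give the expected precision of the arm contrast with its cluster assumptions.

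Cost: no new assessments or participants, because Table 1 and Table 3 already schedule these outcomes in both arms at weeks 0 and 17. The analysis set, the model and the power statement all change, and the result will be less precise than the pooled test suggests.
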